#### Ascertainment of outcomes (see Table 1 Data Collection Points)

**Table 1 T1:** Data Collection Points

***Data collection**	**Baseline**	**Discharge**
Subject demographics	**X**	
Previous falls/medical history	**X**	
Cognitive ability (30 Point MMSE)	**X**	**X**
Quality of Life (EuroQol EQ-5D)	**X**	**X**
Activities of daily living (Barthel Score)	**X**	**X**
Discharge Destination		**X**
Length of stay		**X**
Fear of Falling Questionnaire (mFES)		**X**
Total number of in-patient falls (collected at the time of the index event)		**X**

##### (a) baseline data

The baseline data collected at recruitment originates from face to face interview between researcher and patient, the patient's medical and nursing notes, and/or carer.

Baseline data includes:

a. Demographic and residential details, reason for admission, time since admission.

b. Any previous history of falls, and any resulting fractures.

c. Mobility and transfer before the illness that precipitated admission, and at the time of recruitment (measured by the Barthel ADL index).

d. 30 point Mini Mental Stare examination (MMSE).

e. Health related quality of life measured using the EuroQol EQ-5D.

##### (b) follow up data

Follow up data are collected one day prior or on the day of discharge.

Follow up data includes:

a. Falls, ascertained from hospital incident reporting forms. The use of these incident forms in NUH to record falls is mandatory and enforced by clinical governance processes. Members of the research team collect copies of hospital incident reporting forms from participating wards. Data such as fall event, time, and place, injuries sustained and subsequent actions taken are recorded. Where a medical opinion has been requested, the outcome is recorded, together with any investigations requested. In addition, aggregated, anonymzed data on falls will be collected from hospital incident reporting forms for the trial wards for the 12 month period prior to the trial commencing. The rate of falls in the period prior to the trial commencing will be compared with the control arm rate of falls during the trial to explore whether the use of sensors increases the rate of falls in the control arm.

b. Transfer/mobility and activities of daily living (Barthel ADL). This information is ascertained from the participant or carer, and/or their medical and nursing notes.

c. Quality of life (EuroQol EQ-5D) ascertained by participant interview. Where a participant is unable to participate in an interview, health related quality of life is ascertained from the carer and named nurse.

d. Fear of falling (mFES), ascertained by participant interview. Where a participant is unable to take part in an interview due to poor cognitive ability, this assessment is coded appropriately and excluded from analysis.

e. Mini Mental State Examination (MMSE), through participant interview. The baseline assessment does not account for any acute delirium secondary to the patient's condition on hospitalization, which may improve with treatment. The change in delirium may have an effect on the risk of falling.

f. Length of stay and residential status on discharge, ascertained from medical records.

Data on resource use will be collected for the economic analysis and will include the costs of investigations and interventions arising from any fall whilst in hospital and the length of stay. These data will be obtained from the medical records. Unit costs will be derived from published sources. The cost of the intervention will include rental costs, plus costs of any sensor failures and cost of installing, cleaning, and responding to sensor alarms. Nursing staff on each ward will be asked to record sensor problems and reasons for sensor removal.

Nurse time taken to respond to sensor alarms will be ascertained from an observational study to measure the content and process fidelity of the intervention. The researchers fitting the bed sensors record the length of time taken to fit sensors.

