## Background

Falls in hospitals are common, ranging from 3 to 14 for every 1,000 bed days [1]. Over 200,000 falls were reported to the National Patient Safety Agency's (NPSA) National Reporting and Learning System (NRLS) in the 12 months from September 2005 to August 2006, with falls data being reported from 98% of organisations providing in-patient services [2]. In-patient falls result in injury and anxiety to patients and large costs to NHS organisations, including the costs of treating injuries, increased hospital stay, complaints and litigation [3-5].

Elderly in-patients are at particular risk of falling with the incidence of falls being almost triple that for community-dwelling older people [6]. Several factors contribute to this including; age, a history of falling, impaired mobility and special toileting needs. People with dementia are more likely than those without it to require hospital admission, and are at least twice as likely to fall [7-9]. Up to 30% of in-patient falls occur during the first 48 hours of the patients' admission and 75% of in-patient falls occur in the first two weeks of hospital stay [7,10,11].

Our hospital audit data are consistent with published data [2] and has shown that more than half (53%) of all in-patient falls in elderly people in acute care settings occurred at the bedside, during transfers or whilst getting up to go to the toilet. In the majority of cases these falls were unwitnessed. Where patients had been advised to call for assistance they were often reluctant to ask for help as they "did "not want to bother the nurses" or were unable to do so because of cognitive impairment.

Prevention of falls is a priority for NHS policy makers and practitioners. The Healthcare Commission has used falls prevention as a focus for inspecting compliance under patient safety [12]. Despite our increasing knowledge of the aetiology and epidemiology of falls, there is a dearth of evidence for effective falls prevention in hospitals [13-15]. There is good evidence for falls prevention in the community dwelling elderly [16-18], but these findings are unlikely to generalise to the acute hospital setting.

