### Participants

All patients admitted to five older persons' care wards are eligible for inclusion into the trial. Patients will be excluded from the study if they were permanently bed bound prior to admission, moribund/unconscious, or receiving end of life care on admission, or if they have previously been included in the study in an earlier admission.

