### Outcome measures

#### Definition of primary and secondary outcome measures

The primary outcome measure is the number of bedside in-patient falls per 1,000 bed days from time of randomisation until the participant is discharged from the ward.

A bedside fall is defined as an unexpected event in which the participant comes to rest on the ground, floor or lower level in the area around the bedside, with the bedside being defined as the area encompassed by the curtained area surrounding the bed. For participants in side rooms, the bedside is defined as the area of the room.

The secondary outcome measures are:

a. Number of injurious in-patient falls per 1,000 bed days, defined as falls resulting in abrasion, bruise, swelling, cut, laceration, dislocation, fracture or muscle sprain or strain.

b. Length of hospital stay.

c. Residential status on discharge.

d. Transfer/mobility score and activities of daily living, measured using the Barthel Index [26].

e. Fear of falling, measured using the Modified Falls Efficacy Scale (mFES) [27] to ascertain any differential fear of falling in the two participant groups due to an increased awareness of a potential for a fall, or a greater sense of safety arising from sensor use.

f. Health related quality of life, measured using the EUROQOL EQ-5D [28].

g. Participant and staff experience of using bed and chair sensors. This sub-study will be reported separately.

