### Analysis

#### Quantitative analysis

Analyses will be undertaken on an intention to treat. Intention to treat analysis is defined in this study as an a priori plan to analyse the data according to the groups to which the subjects were randomised regardless of the treatment they received.

Fall rates for each group will be expressed as number of bedside falls per 1,000 bed days. The number of bedside falls per patient will be compared between groups using Poisson regression allowing for over dispersion, with length of stay in days as an offset. Crude models containing intervention group only will be fitted initially, whilst additional models will adjust for the effects of age, MMSE and mobility/transfer scores. Interactions between each of these three variables and treatment group with respect to our primary and secondary outcome measures will also be examined, with covariates dichotomised where necessary. For other secondary outcome measures, groups will be compared using the independent samples t-test for continuous outcomes (or Mann-Whitney U test if assumptions for using the t-test are not satisfied following appropriate transformations of the data) and the chi-square test for binary/categorical outcomes. The rate of falls in the trial wards in the 12 months prior to the trial commencing will be compared with the rate of falls in the control arm during the trial using Poisson regression, allowing for overdispersion as appropriate. A significance level of p < 0.05 will be used for all analyses.

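### The check on whether sensors worsen falls among controls compares two unlike rates, so its no-effect ratio is not known to be 1 and its bias may go either way

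*Protocol article*

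**What the plan says.** **The comparison.** The protocol article, under Ascertainment of outcomes, (b) follow up data, states that "data on falls will be collected from hospital incident reporting forms for the trial wards for the 12 month period prior to the trial commencing", in aggregated and anonymised form. This rate "will be compared with the control arm rate of falls during the trial", and the purpose is "to explore whether the use of sensors increases the rate of falls in the control arm". The Quantitative analysis section repeats the comparison, "with the rate of falls in the control arm during the trial using Poisson regression, allowing for overdispersion as appropriate", and sets a 5% significance level for all analyses. Neither section restricts the prior-year data to eligible patients, aligns time since admission or adjusts for case mix.

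**Who and what the control rate covers.** Under Outcome measures, primary-outcome falls count "from time of randomisation until the participant is discharged from the ward". Under Participants, "Patients will be excluded from the study if they were permanently bed bound prior to admission"; so are those who are moribund or unconscious, receiving end-of-life care, or enrolled at an earlier admission. Consent, by the patient or a proxy, is required. Time since admission is recorded as a baseline item, but no expected value is given.

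**Background to the threat.** The Blinding section names the risk that nurses attend preferentially to patients with sensors, and reports that dummy sensors were tried and abandoned. It assigns any effect on control-group care to a qualitative sub-study. The Background section says "Up to 30% of in-patient falls occur during the first 48 hours" of admission.

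**The concern.** Both arms share wards and nurses, and the nurses are unblinded. If alarms draw attention away from controls, control falls rise and the randomised contrast shows an apparent sensor benefit. The two arms alone cannot reveal this, so the before-after comparison is the only quantitative look at it.

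The comparison sets an all-patient, whole-ward-stay rate against a selected-patient, part-stay rate. Two differences act at once:

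- **Part of the stay.** If falls cluster early and participants enter some time after admission, the control rate is lower than the ward rate even when nothing has changed.
- **Population.** If excluded patients rarely fall but contribute bed days, the control rate is higher than the ward rate even when nothing has changed.

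A null result could be mistaken for reassurance, and a significant rise could be mistaken for harm.

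**Working it through.** **Inputs from the protocol article.** Bedside falls 8.0 per 1,000 bed days, mean stay 19 days, 905 participants per arm, overdispersion 1.5 (Sample size); as many as 30% of in-patient falls in the first 48 hours (Background); 1:1 allocation (Randomisation).

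**The plan's own figure.** 8.0/1,000 × 19 = 0.152 falls per patient, which agrees with the stated 0.15. The spillover check itself has no stated size or power.

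**Step 1: part of the stay.** Let f be the share of falls before randomisation, d the days to randomisation and L the mean stay. With time at risk also counted from randomisation, the ratio expected with no spillover is (1 − f) / ((L − d)/L). It does not depend on the level of the rate. Assume d = 2 and L = 19:

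| f | Control rate per 1,000 | Ratio to 8.0 | True rise that would show as 1.00 |
|---|---|---|---|
| 30% | 0.70 × 0.152/17 = 6.26 | 0.78 | 28% |
| 25% | 0.75 × 0.152/17 = 6.71 | 0.84 | 19% |
| 20% | 0.80 × 0.152/17 = 7.15 | 0.89 | 12% |
| 15% | 0.85 × 0.152/17 = 7.60 | 0.95 | 5% |

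If falls were spread evenly, 2/19 = 10.5% would fall in the first 48 hours and the ratio would be 1.00. If randomisation came at 24 hours with 15% of falls before it (assumed), the ratio is 0.85/(18/19) = 0.90, which masks about 11.5%.

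**Step 2: population.** Let e be the share of ward bed days belonging to excluded patients, assumed not to fall. The eligible rate is then 1/(1 − e) times the ward rate: 1.05, 1.11 and 1.25 for e = 5%, 10% and 20%. The documents give no value for e.

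**Step 3: both together.** Expected ratio with no spillover, randomisation at 48 hours:

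| f | e = 0 | e = 5% | e = 10% | e = 20% |
|---|---|---|---|---|
| 30% | 0.78 | 0.82 | 0.87 | 0.98 |
| 20% | 0.89 | 0.94 | 0.99 | 1.12 |
| 15% | 0.95 | 1.00 | 1.06 | 1.19 |

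The no-effect ratio lies on either side of 1 within this range.

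**Step 4: consequence at the unfavourable end.** Assume five wards of 20 to 28 beds at full occupancy (bed numbers are not in the documents), 905 controls with a mean stay of 19 days, and variance of the log rate ratio 1.5 × (1/E0 + 1/E1), where E0 and E1 are the expected falls before the trial and among controls. A true 28% rise in bedside falls would be declared a significant rise with probability 0.56 to 0.61 in a like-for-like comparison. With the 0.78 mismatch the probability is about 0.025, which is chance level.

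**The case against.** - **The direction is not established.** A reader might infer that the check is built to hide harm. The documents do not support that: Step 3 shows near-cancellation (0.99 with f = 20%, e = 10%) and false alarm (1.12 with f = 20%, e = 20%) as readily as masking. This objection stands.
- **The 28% is an upper illustration.** The 48-hour delay is assumed, and 30% is the protocol's upper figure. It refers to all in-patient falls and to time since admission, not to bedside falls or time on the trial wards. If part of the first 48 hours is spent elsewhere, those falls are missing from the ward rate too and the gap shrinks. This stands.
- **The check is exploratory and not alone.** It is worded as exploration, the 5% level is a blanket rule, and the qualitative sub-study looks at control-group care. This stands and limits the importance of the point. The sub-study does not measure control-arm fall rates, however.
- **Adjustment might be set out elsewhere.** The level of aggregation is not stated, incident forms record time and place, and a fuller document may say more. This stands only in part. The two comparators are fixed in two sections of the article, and forms describe only patients who fell. Alignment would also need bed days split by eligibility and time since admission.
- **A ward-level replacement dilutes the signal.** Participants would contribute 2 × 905 × 19 = 34,390 bed days. With 20 to 28 beds per ward, full occupancy and 27 months of recruitment, that is about 42% to 30% of ward bed days, so a 28% rise confined to them would show as about 12% to 8%. The force of this is limited, because non-participants have no sensors and are exposed to the same diversion of attention.

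**Conclusion.** The point holds in this form: the planned comparison is not like for like, the ratio expected with no spillover is not known to be 1, and neither a null nor a significant result can be read as evidence about spillover. Masking is the direction that matters for safety. Early falls alone could hide a true rise of 5% to 28%, given randomisation at 48 hours and 15% to 30% of falls before it. The net bias may be smaller, nil or reversed, depending on the bed-day share and fall risk of excluded patients, which the documents do not give.

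Two stronger readings should be resisted. The documents do not show that the check will conceal harm, nor that any observed sensor benefit would be an artefact. The randomised comparison, its sample size and its analysis do not depend on this check.

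**What to change.** 1. Collect for the trial period the same aggregated data as for the prior 12 months: falls and occupied bed days by ward and month, for all patients.
2. In the trial-period totals, remove the sensor arm's falls and bed days and give control participants weight 2. Allocation is 1:1, so this estimates the ward rate had every participant been a control while sensors were in use, over the same population and days as the prior-year rate.
3. Compare the two periods by Poisson regression with ward and calendar-month terms, keeping the allowance for overdispersion. Use robust or bootstrap standard errors that account for the weighting: doubling a count C gives variance 4Var(C), whereas treating the doubled count as ordinary Poisson data assumes 2Var(C).
4. Report the result as an exploratory before-after comparison, still open to calendar and reporting changes.
5. If the planned comparison is kept instead, state that it can neither show nor exclude spillover.

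**Cost.** A small amount of extra aggregate data and analysis. Incident forms are already collected on these wards, and prior-year bed-day totals are needed in any case. The primary analysis does not change.

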### Measuring content and process fidelity of the intervention

It is important to be able to demonstrate the extent to which the bed sensors are used in the study (content fidelity) and the way in which they were used (process fidelity). We record the number of participants who do not receive the allocated intervention and reasons for this. Nursing and research staff are asked to record sensor problems and reasons for sensor removal. In order to assess process fidelity, an observational study will be conducted to monitor nurse response rates and time taken to respond, false alarms and improper use of the sensor (e.g. not re-setting the transmitter after an alert). Staffing levels will also be recorded for observation periods to explore whether ability to respond varies with staffing levels. An observer will be provided with a pager identical to those provided to the nurses and will record each alert, the response to each alert, the time taken to respond, the time taken to attend to the patient, whether it was a false alarm or not and improper use of the sensor. Observations will be undertaken over a random sample of days and time periods (two days every 6 months), covering each of the five wards, over the study period.

### Withdrawals

Participants are free to withdraw from the trial at any stage. Participants, who decide to withdraw once recruited to the study, if allocated to a sensor, will have the sensor removed and further data collection from that point stopped. Participants, if allocated to a sensor, in whom it is deemed are at risk of harm resulting from the sensor equipment (for example in cases of confusion where the participant mis-handles the sensor equipment), will have the sensor removed and further data collection from that point stopped.

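### Stopping data collection when a sensor is removed for risk of harm truncates primary-outcome follow-up in the sensor arm only, in conflict with the outcome window and the intention-to-treat aim

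*Protocol article*

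**What the plan says.** The Withdrawals section of the protocol article contains two rules.

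- **Voluntary withdrawal.** "Participants are free to withdraw from the trial at any stage". The sentence that follows covers removing the sensor and ending data collection for those who choose to leave the study.
- **Risk of harm.** "Participants, if allocated to a sensor, in whom it is deemed are at risk of harm resulting from the sensor equipment" are the group concerned. The example given and the consequence are: "in cases of confusion where the participant mis-handles the sensor equipment), will have the sensor removed and further data collection from that point stopped". This decision is made about the participant and is not a withdrawal of consent.

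Other sections bear on the second rule:

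- The primary outcome (Definition of primary and secondary outcome measures) is the "number of bedside in-patient falls per 1,000 bed days from time of randomisation until the participant is discharged from the ward".
- Quantitative analysis defines intention to treat as a plan to "analyse the data according to the groups to which the subjects were randomised regardless of the treatment they received", and compares falls per patient "using Poisson regression allowing for over dispersion, with length of stay in days as an offset".
- Under (b) follow up data, falls come from incident forms whose use is mandatory: "Members of the research team collect copies of hospital incident reporting forms from participating wards". Length of stay comes from medical records.
- The Background says that people with dementia are "at least twice as likely to fall" compared with people without it.

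**The concern.** The risk-of-harm rule turns the stopping of a device into the end of outcome measurement. Only someone with a sensor can trigger it, so it shortens follow-up in one arm. Its only example is confusion, and the Background links dementia to a higher risk of falling, so the person-time lost may well be high-risk person-time. Comparable patients in the control arm are followed to ward discharge and all their falls count.

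At stake is the comparison that randomisation was meant to protect. If high-risk days and their falls leave one arm only, a sensor with no effect can appear to reduce bedside falls. No later analysis can restore falls that the protocol says not to collect.

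**Working it through.** **1. The sections side by side.** The outcome window ends at ward discharge and makes no exception for sensor removal. The analysis principle disregards treatment received. The risk-of-harm rule ends data collection because treatment stopped. For a participant removed under that rule, falls between removal and discharge belong to the outcome as defined but are not collected. Truncated records can still be analysed by randomised arm. An analysis of everyone randomised over the full window cannot be done.

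**2. The plan's own figure.** Inputs from Sample size: 8.0 bedside falls per 1,000 bed days, 19-day mean stay, rate ratio 0.65, 80% power, alpha 0.05 (two-sided assumed), dispersion 1.5, 905 per arm. The mean number of falls per patient is m = 8.0 × 19 / 1000 = 0.152, which the article rounds to 0.15. A Poisson regression formula with separate null and alternative variances is

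n = 1.5 × [1.96 × √(2/m) + 0.8416 × √(1/m + 1/(0.65m))]² / (ln 0.65)².

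It gives 911.5 at m = 0.150, 905.4 at m = 0.151 and 899.5 at m = 0.152. The stated 905 reproduces, and this point does not affect it.

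**3. Apparent rate ratio when the true ratio is 1.** The article gives no removal fraction, so these inputs are assumptions:

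- q = share of the sensor arm removed, 2% to 20%.
- k = fall rate of removed participants relative to the others. The main case uses 2, suggested by the Background figure for dementia.
- f = share of the stay observed before removal, set at 0.25.
- Constant hazard, equal mean stay in removed and other participants, and by randomisation the same share q of such patients in the control arm.

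Formulas:

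- Control rate (relative): (1 − q) + qk
- Sensor-arm falls counted: (1 − q) + qfk
- Sensor-arm exposure: (1 − q) + qf if cut at removal, or 1 if full stay is the offset

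Example with q = 0.10: the control rate is 0.90 + 0.20 = 1.10, falls counted are 0.90 + 0.05 = 0.95, and cut exposure is 0.90 + 0.025 = 0.925. The rate ratio is 0.95 / 0.925 / 1.10 = 0.934 with exposure cut, and 0.95 / 1.10 = 0.864 with the full stay.

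| Removed (q) | RR, exposure cut | RR, full stay |
|---|---|---|
| 2% | 0.985 | 0.971 |
| 5% | 0.965 | 0.929 |
| 10% | 0.934 | 0.864 |
| 20% | 0.882 | 0.750 |

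**4. Chance of falsely favouring sensors.** A Wald approximation with 905 per arm is Φ(−1.96 − ln(RR)/SE), where SE = √[1.5/905 × (1/0.152 + 1/(0.152 × RR))]. For RR = 0.934, SE = 0.150 and the chance is about 7%, against 2.5% with no distortion. For 2%, 5%, 10% and 20% removed it is about 3%, 4%, 7% and 13% with exposure cut, and 4%, 7%, 16% and 44% with the full stay.

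**5. Sensitivity of the direction.**

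- *k = 1 (average risk).* With exposure cut, RR is exactly 1.000. With the full stay it is still below 1 (0.925 at q = 10%), because falls are lost while bed days remain.
- *k = 0.5.* With exposure cut, RR is 1.038 at q = 10%, which is against sensors.
- *Very early removal.* The Background puts up to 30% of falls in the first 48 hours of admission. Take removal at 2 of 19 days, with 30% of falls already counted and exposure cut. At q = 10%, RR is 1.021 for k = 1, 0.958 for k = 2 and 0.906 for k = 3. The direction changes at a k of about 1.3 to 1.4.
- *Front-loaded falls.* Suppose, as an assumption, that 40% of falls precede one quarter of the stay. With k = 2 and exposure cut, RR is (0.90 + 0.10 × 2 × 0.40) / 1.10 / 0.925 = 0.963 at q = 10%.

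**The case against.** The case against a strong statement of this point has five parts.

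- **Confusion is only an example.** A reader might infer that most of those removed would be confused, high-risk patients. The article gives no frequency and does not say so. This objection stands.
- **Intention to treat is not ruled out to the letter.** A reader might infer that the stated analysis is impossible. By the article's own definition, truncated records can be analysed in the randomised arm. What is lost is complete follow-up to ward discharge. This stands.
- **Not every removal ends follow-up.** The sections on resource use and on fidelity record sensor problems and reasons for removal without saying that data stop. Voluntary withdrawal is open to everyone, and its wording about sensor allocation may govern only taking the sensor away, so control withdrawals may end data collection as well. Only the risk-of-harm rule is clearly one-sided.
- **Bias towards sensors is not certain if exposure is cut.** The Background figure compares people with and without dementia, but those who remain include confused patients, who may enter by proxy consent. If 40% of those remaining had dementia (an assumption), k would be 2/1.4 = 1.43 and the 10% case would move from 0.934 to 0.970. This stands as a limit on size and direction.
- **The largest figures need a particular reading.** The full-stay results require falls collection to stop while length of stay is still recorded. The rule stops data collection in general and does not exempt length of stay. On the other side, the analysis section names length of stay as the offset and makes no adjustment for removal. The text supports neither reading outright.

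The placement of the pads (the bed pad under the mattress, the chair pad possibly under a cushion) may also make mishandling uncommon, which is why the table starts at 2%. None of this removes the conflict between sections.

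**Conclusion.** The point holds in limited form. One rule in Withdrawals truncates primary-outcome follow-up in the sensor arm alone, through a post-randomisation event plausibly related to fall risk. It contradicts the outcome window and defeats the purpose of the intention-to-treat analysis.

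The size cannot be known from the article. Under the assumptions of a true ratio of 1, double risk, removal at one quarter of the stay and a constant hazard, the apparent rate ratio runs from 0.985 (2% removed) to 0.88 (20%) with exposure cut at removal, and from 0.97 to 0.75 with full length of stay as the offset. With the full-stay offset, the distortion always favours sensors once post-removal falls are lost. With exposure cut, it is nil at average risk, smaller if falls are front-loaded, and can reverse with very early removal and only slightly raised risk. A reader should not conclude that the trial is certain to be biased towards sensors, or by how much.

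**What to change.** Separate removal of the sensor from the end of follow-up:

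- After removal for risk of harm, keep counting falls from incident forms and bed days from medical records until ward discharge, and analyse the participant in the randomised arm.
- Stop data collection only when the participant or proxy withdraws permission for data use. State one rule for both arms, and in those cases set the offset to the days observed.
- Report sensor removals, with reasons, as a fidelity result.

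No change to when a sensor is removed is proposed.

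The cost is a sentence in Withdrawals, a clause on the offset, and a line on the withdrawal form that distinguishes stopping the sensor from withdrawing permission. Falls and bed days come from routine sources that do not depend on a sensor, so no extra visit is needed. Continuing the interview-based discharge measures (EQ-5D, mFES) would take staff time, and this repair of the primary outcome does not require it.
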